#### Interim analyses {21b}

None. The risks of harm from the current trial and intervention are low and no greater than those for normal school teaching activities.

#### Methods for additional analyses (e.g. subgroup analyses) {20b}

At the individual level, we will control for any effects of sex, age, and Pupil Premium^2^ eligibility. At the group level, we will control for any effects of school and school class group. Any group differences will be interpreted in the light of information about process adherence and teacher engagement, as reflected in the teacher survey (see Additional file 1: Appendix 3).

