### Participant timeline {13}

The trial runs over the 2021–2022 school year. Schools nominate eligible year groups for participation. Cluster randomisation will be at the level of paired teaching class groups, within-school. For example, a school chooses year 1 to participate. Year 1 contains two classes, 1A and 1B. At random, class 1A is assigned to the control group and 1B to the experimental group. See Fig. 1. Schools can choose the timing of intervention delivery separately for each pair of classes. Therefore, different class pairs can have different intervention timings.

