### Statistical methods

#### Statistical methods for primary and secondary outcomes {20a}

For each participant, pre/post-intervention difference will be calculated for each primary measure, plus the normalised sum of primary measures (to represent overall ‘curiosity and confidence’). Each set of data will be analysed using regression models with pre-post difference as the outcome. Secondary measures will be examined using the same methods as primary measures. The number of clusters is too small to analyse using a multi-level model, however school and class will be included as a covariate.

For each participant, data will be collected at baseline and follow-up. The main outcomes (dependent variables) will be individual scores in WTT, enjoyment/engagement (from facial expression), and verbal engagement at follow-up. The difference in scores between the intervention and the control group will be calculated for each of the primary measures, plus an overall score consisting of the sum of primary measures which represents overall curiosity and confidence. Each set of data will be analysed using two level regression models (where appropriate), to take into account the clustering of children within schools. The analysis will be adjusted for baseline scores.

The intervention should benefit those children most in need of support. To reflect this in our analysis, we will split the participants into three sub-groups according to their score on a given measure at baseline (low, mid, high). Each grouping will cover 1/3 of the range for that measure. It is important that any benefits be observed in the low and/or mid groups and not just be driven primarily by the high group. High scores are considered desirable in all measures.

The liking secondary measure will be examined using the same regression methods.

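### Classes are randomised in pairs, but the planned group terms are school and class: class is aliased with arm, school is coarser than the pair, and the pair is never named.

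*Protocol article*

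**What the plan says.** **Design.** Participant timeline {13}: "Cluster randomisation will be at the level of paired teaching class groups, within-school". Its example takes the two classes of one year group: "At random, class 1A is assigned to the control group and 1B to the experimental group". Schools choose delivery time pair by pair, so "different class pairs can have different intervention timings". Under Eligibility criteria {10} a school chooses which of three year groups take part, so it may enter more than one pair.

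**Analysis.** Section {20a} gives two descriptions. The first is single-level: "The number of clusters is too small to analyse using a multi-level model, however school and class will be included as a covariate". The second uses "two level regression models (where appropriate), to take into account the clustering of children within schools". Section {20b} adds: "At the group level, we will control for any effects of school and school class group", and for children: "At the individual level, we will control for any effects of sex, age, and Pupil Premium" eligibility. The list headed Independent measures has arm, date of birth, sex, Pupil Premium, school and class. The pair, the year group and the delivery period appear in none of these places.

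**The concern.** With few classes, pairing is the main protection the design offers: it takes school, and in the protocol's example year group, out of the arm comparison, along with the pair's delivery time. The analysis keeps that benefit only if it compares arms within pairs.

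The two group terms named sit on either side of the pair. Class is finer and is confounded with treatment. School is coarser and pools pairs that may differ in year group and in time of testing. An analyst who follows the text either meets a model that cannot estimate the arm effect or has to drop class. Nothing in the protocol then points back to the pair. At stake are whether the primary contrast can be estimated at all, and whether its interval has the right width.

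**Working it through.** **Inputs from the protocol article.** Pairs of classes within a school, one class per arm ({13}); 400+ children (Abstract); five named schools ({9}); difference 0.5 foods, SD 1.38, 90% power, 160 per arm ({14}).

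**The plan's own figure.** With two-sided alpha 0.05 (assumed; not stated), n per arm = 2 × [1.38 × (1.960 + 1.282)/0.5]² = 160.08, so 160 is reproduced. The formula has no term for class or pair. The effect size it implies is 0.5/1.38 = 0.36 SD, used below.

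**Assumed, not in the document.** 8 pairs in 5 schools (three schools with two pairs, two with one), 16 classes of 25, 400 children, total variance 1. Pair and class-within-pair variance shares are varied and stand for what is left after baseline and age adjustment.

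**Step 1: school and class as fixed covariates.** The arm indicator is the sum of the indicators of the intervention classes.

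| Terms | Columns | Rank |
|---|---|---|
| arm + class | 17 | 16 |
| arm + school + class | 22 | 16 |
| class alone | 16 | 16 |
| class + pair | – | 16 |
| arm + pair | 9 | 9 |

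Adding arm to class leaves the rank at 16, so the arm effect is not estimable. Adding pair to class also leaves it at 16: class effects already absorb every pair difference, so adding pair while class stays repairs nothing. The aliasing holds for any number of classes, because each lies in one arm.

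**Step 2: children within schools, no class term.** Approximated by child-level regression with school effects, 10,000 simulated trials per row.

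| Pair share | Class share | True SD of arm estimate | Mean model SE | 95% coverage, school | 95% coverage, pair instead |
|---|---|---|---|---|---|
| 0.02 | 0.02 | 0.119 | 0.099 | 89.7% | 89.5% |
| 0.05 | 0.05 | 0.146 | 0.097 | 80.8% | 80.2% |
| 0.10 | 0.05 | 0.145 | 0.096 | 80.7% | 79.6% |
| 0.05 | 0 | 0.098 | 0.098 | 95.2% | 95.0% |

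The interval is too narrow as soon as classes vary, and exchanging school for pair at child level does not cure it.

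**Step 3: class as the unit of error, school only.** Take pair share 0.05 and class share 0.02. The error variance of a class mean is 0.02 + 0.93/25 = 0.0572. With arm and school fitted to 16 class means, 10 residual degrees of freedom remain: 7 within pairs, with mean square 0.0572, and 3 between pairs within schools, with mean square 2 × 0.05 + 0.0572 = 0.1572. Pooled: (3 × 0.1572 + 7 × 0.0572)/10 = 0.0872.

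- SE used, school only: √(2 × 0.0872/8) = 0.148
- SE with pair: √(2 × 0.0572/8) = 0.120, which is also the true SD

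Simulation agrees. The mean SE is 0.143 with school against 0.115 with pair (true SD 0.120), the half-width 0.319 against 0.273, and the coverage 97.4% against 94.9%.

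Across pair shares, with class share 0.02 and true effect 0.36 SD (4,000 trials per setting):

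| Pair share | SE, school only | Power, school only |
|---|---|---|
| 0 | 0.119 | 76% |
| 0.01 | 0.123 | 73% |
| 0.03 | 0.134 | 67% |
| 0.05 | 0.143 | 62% |
| 0.10 | 0.163 | 50% |

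With pair fitted, the SE is about 0.116 and power about 73% throughout. Type I error with school only falls from 4.9% to 1.2% across the table, against about 5% with pair.

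**Break-even.** Squared half-widths are equal when 1 + 0.6 × (pair variance)/(class-mean error variance) = (t₇/t₁₀)² = (2.365/2.228)² = 1.127. That gives pair variance = 0.21 × 0.059 ≈ 0.012, in line with the simulated break-even near 1%.

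**The case against.** A reader might infer that, because the analysis adjusts for school and not for the pair, the planned interval is simply too wide. The documents do not support that. The quoted sentence names class as well as school, and class effects absorb all differences between pairs, so none stays in the error; the trouble with that model is that the arm effect cannot be estimated. Under the other description the interval is too narrow, not too wide. Conservatism arises only in an analysis the protocol does not describe, one with class as the unit of error and school as the only group term.

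Three further points have force. The number of pairs per school is not given, and where a school enters one pair, school and pair coincide. Age and baseline scores are adjusted for and will take up part of any year-group difference. The gain in Step 3 rests on variance shares the document does not supply, and below about 1% adding pair costs a little power.

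It can also be said that a blocking term is the kind of detail left to an analysis plan. This protocol, however, does not leave the group terms open. It lists them in three places, and the listed terms cannot do the job. Because class has to leave the fixed part of the model, school is the only group term that remains. One pair in each of the five named schools would give 10 classes and 400/10 = 40 consenting children per class. So unless further schools join or classes are that large, some school must enter more than one pair.

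**Conclusion.** The point holds in this form: the randomisation block is missing from the analysis, and neither planned group term can stand in for it. That class is aliased with arm follows from the design alone and needs no assumption. The other consequences run in opposite directions, depending on how an analyst resolves the text. A child-level analysis with school only is too narrow (coverage about 81–90% at class variance 2–5%). A class-level analysis with school only is too wide when pairs within a school differ: 0.319/0.273 = 1.17, or 17% wider at 5% pair and 2% class variance, with power 62% against about 73%. Both sizes rest on the assumed layout and variance shares, and the second also on some schools entering more than one pair. The document should be changed, mainly because the remedy settles all three problems and costs almost nothing.

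**What to change.** In {20a} and {20b}:

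1. Remove class as a fixed covariate.
2. Replace school with class pair as the fixed blocking term. Pair is nested in school, so school is absorbed.
3. Estimate the arm effect within pairs with class as the unit of error: either a paired analysis of class means adjusted for baseline and the child-level covariates, or a child-level model with a random class effect and a small-sample correction. Base the degrees of freedom on the number of pairs.
4. Replace the two descriptions in {20a} with this single model.

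Add class pair to the Independent measures list. Step 2 without steps 1 and 3 would leave the arm effect inestimable or the interval too narrow.

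**Cost.** Wording only; pair membership is known from randomisation and no new data are needed. In the illustration the residual degrees of freedom fall from 10 to 7 relative to a class-level analysis with school. If pairs within a school do not differ at all, power drops by about 3 to 4 points (76% to about 73%).

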#### Methods in analysis to handle protocol non-adherence and any statistical methods to handle missing data {20c}

Analysis will follow intention-to-treat principles for all participants who complete the intervention. Adherence will be assessed via a teacher survey and supported via personal contact with participating teachers and school visits by researchers to observe delivery of the intervention and offer support/guidance where necessary. A participant’s data will be excluded if it is not possible to gather post-intervention data.

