#### Individual inclusion criteria

All children in experimental group classes will receive the intervention, delivered as part of regular school teaching. Children in the control group will receive normal teaching with no intervention. No particular level of spoken English is required. However, only children with opt-in caregiver consent will contribute data to the study.

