### Outcomes {12}

The observational scenario is a tasting activity done in small groups (see the “Plans for assessment and collection of outcomes {18a}” section). The test activity will conducted < 6 weeks before (baseline) and < 6 weeks after intervention delivery is completed. Analysis metric for all measures is follow-up scores, adjusted for baseline, for all children.

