**Fig. 1 Fig1:**
[figure not shown]
Participant timeline and cluster randomisation

Teachers will be instructed to ensure Flavour School delivery respects class delineations, to minimise contagion. The control group receives no intervention (i.e. the standard curriculum). Pre- and post- intervention data collection is conducted for both the experimental and control groups. The control group can receive the intervention after post-intervention data collection is complete, at the school’s discretion.

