#### Plans to promote participant retention and complete follow-up {18b}

Participants who leave the school/class during the trial will not be included in the trial. The intervention is enjoyable and is integrated into school-time teaching. No follow-up measures are currently planned, due to shortening of the trial to accommodate COVID-19-related time pressures.

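### The analysis is called intention-to-treat but is limited to participants who finish the programme, a restriction that, applied literally, can exclude children only from the intervention arm

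*Protocol article*

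**What the plan says.** Section {20c} of the protocol article sets the analysis population in one sentence: "Analysis will follow intention-to-treat principles for all participants who complete the intervention". It then says "Adherence will be assessed via a teacher survey", backed by contact with teachers and school visits, and adds a separate rule for missing outcomes: "A participant’s data will be excluded if it is not possible to gather post-intervention data". No definition of completion is given, for a child or for a class.

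Four other places bear on who is analysed:

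- Individual inclusion criteria: "Children in the control group will receive normal teaching with no intervention".
- Participant timeline {13}, in the text after Fig. 1: "The control group can receive the intervention after post-intervention data collection is complete, at the school’s discretion".
- Retention {18b}: "Participants who leave the school/class during the trial will not be included in the trial".
- Outcomes {12}: "Analysis metric for all measures is follow-up scores, adjusted for baseline, for all children".

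Additional analyses {20b} says that group differences will be read against what the teacher survey shows about adherence and engagement. It names no exclusion on those grounds.

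**The concern.** Intention-to-treat means analysing participants in the arm to which they were randomised, whatever they received. A set limited to those who complete the intervention is a per-protocol set, so the sentence contradicts itself on the population for every primary measure.

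The restriction is also not symmetrical. Only one arm has a programme to complete before the outcome is measured, so a literal application would compare a selected intervention group with an unselected control group. Randomisation is by paired classes within a school, so dropping a whole class would also leave its partner without a comparator. A reader of the trial report would see an intention-to-treat label and would not expect either of these things.

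**Working it through.** **Step 1: which arm can the clause act on?**

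| Rule | Section | Arms it can act on |
|---|---|---|
| Must complete the intervention | {20c} | Intervention only, read literally: controls get the programme, if at all, after outcome measurement |
| No post-intervention data | {20c} | Both |
| Left school or class | {18b} | Both |

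The last two rules already cover loss to follow-up. The completion clause is therefore either redundant (if it means only that the child was still present at the end) or an extra filter on one arm.

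**Step 2: the protocol's own figure.** Sample size {14} gives a difference of 0.5 foods, SD 1.38, 90% power and 160 per arm. Alpha is not stated; two-sided 0.05 is assumed because it reproduces the figure:

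n = 2 × [1.38 × (1.960 + 1.282) / 0.5]² = 160.08 per arm.

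This agrees with the stated 160 (power 0.900 at 160 per arm). The sample size is not in dispute here; it supplies the scale for Step 3.

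**Step 3: how large could the effect of the filter be?** The documents give no completion rate and no link between completion and outcome. Both are assumed:

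- d = share of the intervention arm removed: 5%, 10%, 20%.
- ρ = correlation of completion with outcome: 0 to 0.5, taken as positive (completers would score higher).
- True effect zero, 160 per arm before removal, no clustering, no baseline adjustment.

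Bias in SD units = ρ × φ(z_d) / (1 − d), where φ is the standard normal density and z_d the d-quantile. Multiply by 1.38 for foods.

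Example, d = 10%, ρ = 0.3: φ(−1.282) = 0.1755; 0.3 × 0.1755 / 0.90 = 0.058 SD; × 1.38 = 0.08 foods.

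| d | ρ | Bias (foods) | Share of 0.5 target | Type I error (nominal 5%) |
|---|---|---|---|---|
| 5% | 0.2 | 0.03 | 6% | 5.4% |
| 10% | 0.3 | 0.08 | 16% | 8.0% |
| 20% | 0.3 | 0.14 | 29% | 14.3% |
| 20% | 0.5 | 0.24 | 48% | 31% |

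With ρ = 0 there is no bias, only lost power: 90% falls to 88.4% at d = 10% and to 86.3% at d = 20%.

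**The case against.** The best defence is that the clause is loose wording for finishing the trial period. No completion threshold exists, so no filter is operational as it stands. Section {20b} uses adherence to interpret results, which suggests that poorly delivering classes were meant to stay in. On that reading the exclusions fall on both arms and the defect is a mislabelled complete-case analysis. This is plausible, but {20c} does not say it, and the missing-outcome rule in the same section already does that job. Even on this reading the sentence has to change.

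A reader might go further and infer that the result will be biased towards benefit because the less engaged teachers and children drop out. The documents do not support that as fact. The programme is delivered to the whole class in ordinary lessons, so individual children do not opt out of it. A class might stop because of COVID-19 disruption, which the protocol anticipates and which has no obvious link to tasting scores. Support for delivery is also planned.

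A reader might also take the Outcomes {12} wording about all children as a flat contradiction. It defines the analysis metric, not the analysis population, so it fits poorly with the completer clause but does not settle the matter.

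The illustrative figures have limits too. The SD comes from a four-food test in children aged 1–3 years, whereas this trial offers nine foods and weights the proportion tasted by a Gusto rating. Baseline adjustment would remove part of any difference already present at the start.

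**Conclusion.** The point stands as a defect in the stated analysis set. Section {20c} contradicts itself, leaves completion undefined and, applied literally, allows post-randomisation exclusions from the intervention arm alone. It also sits badly with {20b}, where adherence informs interpretation and does not exclude anyone.

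The consequence is less certain than the defect. Bias arises only if completion is related to outcome; its direction is plausibly towards benefit but is not established. The range of roughly 0.03–0.24 foods (6–48% of the target difference) rests wholly on the assumed d and ρ and on an SD that is not on this trial's outcome scale. At its low end the effect is trivial. It shows that the clause could matter, not how much it will.

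**What to change.** 1. In {20c}, delete the closing clause that restricts the analysis to completers.
2. Define the primary set as all consented children in randomised classes who have follow-up data, analysed by the class's allocated arm whatever amount of the programme was delivered. Describe it as an as-randomised analysis of children with observed outcomes; with missing outcomes still excluded, it is not full intention-to-treat and should not be labelled so.
3. Hold the follow-up session in classes that stop delivery early. Outcomes {12} times follow-up from the completion of delivery, so such a class currently has no stated follow-up point.
4. Keep any completer analysis as a labelled sensitivity analysis, with completion defined from the teacher survey.
5. Reconcile {12}, {18b}, {20b} and {20c} so that they describe one population.

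The cost is mostly rewording, plus follow-up sessions in any class that stopped early. The estimated effect may be smaller than among completers, because it would then include classes where delivery lapsed.

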#### Plans to give access to the full protocol, participant level-data and statistical code {31c}

Open access to full protocol and code is anticipated. Children’s video data will be kept private by default. Anonymised measures and statistical data will be open access via University of Leeds Library Data Service.

### Oversight and monitoring

#### Composition of the coordinating centre and trial steering committee {5d}

The co-ordinating centre is the School of Food Science and Nutrition, at the University of Leeds. The lead researcher is conducting data collection and the day-to-day running of the trial. The PI, together with a project mentor, are overseeing and supporting the lead researcher.

#### Composition of the data monitoring committee, its role and reporting structure {21a}

This is a small trial of a food education programme. Both scale and risk are small enough that a dedicated data monitoring committee has not been judged proportionate. The lead researcher will be the primary data handler, overseen by the PI. The trial is funded by an EU H2020 grant.

#### Adverse event reporting and harms {22}

Adverse events/incidents in schools will be logged through the school’s standard reporting procedures, and the study team informed to log incidents in the study risk assessment and health and safety documentation. It is not anticipated that adverse incident(s) will result in discontinuation of the study. It is possible that the trial will be discontinued or postponed due to potential disruption to schools arising from the coronavirus pandemic.

### Frequency and plans for auditing trial conduct {23}

There are no plans for auditing of trial conduct, due to the small size and low risks of the trial.

#### Plans for communicating important protocol amendments to relevant parties (e.g. trial participants, ethical committees) {25}

Changes to the protocol will be submitted to the supervising ethical committee as an amendment. Participating schools and teachers will be informed directly by email. Any changes will be submitted to Trials journal as updated versions of the protocol and to ISRCTN as updates of the OASES study account.

